**Introduction**

At least 1 million nasogastric (NG) tubes are used in the UK each year, often for supplementary feeding [1]. They allow liquid feed to be passed directly into the stomach without requiring the patient to swallow. The National Patient Safety Agency issued guidelines recommending aspirate pH is tested before every feed and at least once every day to check nasogastric tube position and prevent harm from feeding into the lungs through a misplaced nasogastric tube.

Current best practice uses pH testing to ensure the tube is correctly positioned in the stomach. An acidic result (pH equal to or less than 5.5) indicates that the nasogastric tube is correctly positioned in the stomach and feeding is safe. If the result is not acidic (pH >5.5), a chest radiograph is indicated to check that the nasogastric tube is positioned in the stomach and not in the lungs [2]. However, up to 42% of hospital inpatients receive antacid medications that render the results of pH test paper falsely negative [3].

The ideal solution would be a test that was accurate despite non-acidic gastric aspirates, safe, point-of-care, and non-ionising. Human gastric lipase is an endogenous gastric enzyme, which starts the digestion of dietary triglyceride in the human stomach [4]. Chief cells secrete human gastric lipase entirely from the gastric fundus [5,6]. Human gastric lipase is relatively stable and its production, unlike the secretion of hydrochloric acid from gastric parietal cells, is not affected by antacid medications [7,8]. One barrier to a single reagent test is that human gastric lipase is inactivated by acidic stomach contents and therefore is unsuitable as a means of determining nasogastric tube position on its own. It has been suggested that a combined test for pH incorporating a gastric enzyme may be significantly more accurate than each in isolation [9]. The objective of this study is to validate a nasogastric tube position test that was compatible with non-acidic gastric aspirates by utilising human gastric lipase to lower the pH of gastric aspirates on pH test paper.

**Study aims**

- To determine the sensitivity and specificity of the lipase/pH test strip
- To determine how many chest radiographs would be avoided if the lipase/pH test strip was used instead of the standard pH test
- To observe in a simulated environment the use of lipase based pH test strip and analyse the perceived usefulness of this test from professional perspective.

**Study design**

**1. Diagnostic Accuracy Study**

*Primary outcome*

Sensitivity of the index test and the reference tests (standard pH test) under cut-off 5.5 with tube sites confirmed by either patient follow up or chest x-rays when applicable.

*Secondary outcomes*

1. Percentage unable to aspirate is measured by the number of patients for whom no aspirate is obtained out of the total number of patients for whom the attempts have been made before either successful aspiration or before chest x-rays has to be requested

2. Number of chest radiographs requested is recorded exactly as described, when aspirates and re-attempts both fail

*Subject selection and setting*

Participants will be recruited from Imperial College Healthcare NHS Trust at both the Charing Cross and St. Mary’s hospital sites. Eligible participants will be identified by the clinical team and recruited by a member of the research team. These will be patients that require nasogastric tube insertion as part of their clinical management such as patients following stroke, gastrointestinal surgery or with head and neck conditions. Therefore the study will be undertaken on the following wards: Charles-Pannett, intensive care, Charing Cross wards 9 west, 9 north, 10 south and 9 south. If it has been determined that a participant lacks the capacity to make a decision for himself, a personal consultee shall be consulted on behalf of the participant. In the event that a personal consultee is not available, a Nominated Consultee shall be consulted to make a decision whether the patient may be a participant in the study.

*Inclusion Criteria*

Patients who require the insertion of nasogastric tubes for supplementary enteral feeding as part of their clinical management

*Exclusion Criteria*

- Patients under the age of 18 years
- Prisoners
- Patients sectioned under the Mental Health Act

*Protocol*

The clinical trial will be a diagnostic accuracy study of two diagnostic tests and will be performed in accordance with the STARD guidelines for diagnostic tests [11]. The index tests will be (i) the novel lipase/pH test strip and (ii) standard pH test strip. The reference test used for comparison will be chest x-ray or where this is not required ‘trial by use’ (any chest x-rays undertaken would be decided and authorised by the participant’s clinical team who are clearly separated from the research team. Undergoing a chest x-ray does not from part of screening for the study and is not a requirement of the study protocol).

Ingenza novel lipase/pH test strip

The test is based on detecting organic acid released from a chemical ester impregnated onto pH paper by the action of human gastric lipase that is stable in gastric juice and resistant towards antacid medications, as well as unlikely to migrate. Ingenza have impregnated enteral pH indicator strips that are in current clinical use with emulsion formulations protected by intellectual property as human gastric lipase substrates. Therefore the novel test strips will provide a positive result in the presence of an acidic environment (pH less than or equal to 5.5) or gastric lipase.

Index testing

The nasogastric tube will be aspirated to obtain a sample of gastric fluid. This will either be immediately following insertion or as part of daily position confirmation that is routinely performed prior to initiation of nasogastric feeding. The aspirate will be used by the healthcare professional, if required, as part of routine care and the remaining sample passed to a member of the research team. The sample will then be used to wet the two index test strips. Two members of the research team will independently assess the results of the test papers at two minutes. If two members of the research team are not available then one member will test the papers and take photographs of the test papers so that a second member of the team can verify the findings. These investigators will be blinded to the results of the reference standard. For standard pH strips a pH of ≤5.5 will indicate correct tube placement and >5.5 indicated incorrect nasogastric tube position. For lipase/pH strip test a positive result will be determined according to the manufacturers recommendations.

Reference Testing

The reference standard test will consist of chest radiography or trial by use if chest radiography is not indicated. Consultant radiologists who will be blinded to the index test results will interpret chest radiographs. Criteria for correct nasogastric tube position on the chest radiograph include a straight vertical course near the midline passing through the carina and not following a bronchus with the tip below the diaphragm on the same side as the gastric bubble.

Patients with a nasogastric tube in situ will be assessed with both the index and reference standard test. The reference standard pH test will be administered first (according to manufacturer’s instructions) followed immediately by the Ingenza enzymatic nasogastric tube position test. The same researcher will perform both tests. The pH test will be performed first as it is known from the pilot study to be the least reliable and so less likely to influence interpretation of the new test. The two tests will be read by the same healthcare worker to minimise inter-reader variability. The standard pH test will be deemed positive if the reader assesses the pH to be greater than 5.5 (a subjective assessment made by comparing the pH strip to a colour intensity chart). If either test is positive (suggesting that a tube is misplaced) then the participant’s clinical team will be informed so that they can confirm correct tube placement before use. Therefore, aside from the potential increase in patients requiring tube position verification by x-ray there will be no change to standard care policy. Patients will be followed up until they have had a gold-standard test to confirm the position of their nasogastric feeding tube. This will either be by x-ray or when x-ray is not indicated ‘trial by use’ of the nasogastric feeding tube.

*Statistics*

We aim to collect data from 145 patients. The sample size is computed based on test validity findings from our earlier trial at the St Mary’s hospital and has 80% power and 5% significance level and includes a 15% allowance for drop-out.

Diagnostic performance will be expressed through sensitivity with 95 % confidence Intervals (95 % CI). Demographic and clinical characteristics will be expressed as percentages for categorical data, and median with interquartile ranges (IQR) for continuous data due to their non-normal distribution.

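### The objective concerns non-acidic aspirates, but the protocol plans sensitivity only over all patients and no direct estimate at pH >5.5

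*Protocol*

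**What the plan says.** The Introduction gives the purpose: "The objective of this study is to validate a nasogastric tube position test that was compatible with non-acidic gastric aspirates". The reason offered is that "up to 42% of hospital inpatients receive antacid medications that render the results of pH test paper falsely negative".

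Study aims puts the accuracy aim without any stratum: "To determine the sensitivity and specificity of the lipase/pH test strip". A second aim is "To determine how many chest radiographs would be avoided if the lipase/pH test strip was used instead of the standard pH test".

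In the Diagnostic Accuracy Study, the primary outcome is "Sensitivity of the index test and the reference tests (standard pH test) under cut-off 5.5", with tube site confirmed by follow-up or chest x-ray. The Statistics paragraph adds: "Diagnostic performance will be expressed through sensitivity with 95 % confidence Intervals (95 % CI"). Neither place separates acidic from non-acidic aspirates or plans a comparison between the strips with an interval.

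The description of the novel strip says that it gives "a positive result in the presence of an acidic environment (pH less than or equal to 5.5) or gastric lipase". Eligibility covers adults who need a nasogastric tube for feeding, with no selection by aspirate pH. One aspirate wets both strips.

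**The concern.** An aspirate at pH 5.5 or below should turn both strips positive, so it carries no information on whether the lipase component works. Only aspirates above 5.5 from correctly placed tubes test what is new about the strip, and they are also the samples that the objective describes. A sensitivity over all patients mixes the two kinds in proportions set by the wards' case mix, which the protocol does not fix.

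The risk is one of interpretation. A high overall figure could be reported as support for use in non-acidic aspirates when most of it comes from samples that ordinary pH paper would also have called gastric.

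**Working it through.** **Inputs from the protocol.** 145 patients including a 15% drop-out allowance (Statistics); the acid-or-lipase rule (novel strip description); both strips on one aspirate (Index testing). The 145 cannot be reproduced, because the expected sensitivities are attributed to an earlier trial and not given. Only the drop-out step can be checked: 123 / 0.85 = 144.7, rounded up to 145. About 123 evaluable patients is therefore used below (145 / 1.15 = 126 under the other convention).

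**Assumptions.** q is the share of correctly placed tubes with aspirate pH >5.5, and L is the novel strip's detection rate in those samples. The protocol gives neither. The 42% in the Introduction is an upper figure for antacid use, not for non-acidic aspirates; it serves here only as one value of q. All evaluable tubes are taken as correctly placed, every acidic sample is taken to turn the novel strip positive, and sensitivity means detection of gastric placement.

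**Pooled sensitivity.** S_new = (1 − q) + qL, and S_pH = 1 − q.

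| q | S_pH | S_new, L = 25% | S_new, L = 50% | S_new, L = 75% |
|---|---|---|---|---|
| 20% | 80% | 85% | 90% | 95% |
| 30% | 70% | 77.5% | 85% | 92.5% |
| 42% | 58% | 68.5% | 79% | 89.5% |
| 50% | 50% | 62.5% | 75% | 87.5% |

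**In counts, n = 123, exact 95% CIs.**
- q = 20% gives 25 non-acidic and 98 acidic samples. If 12 of 25 are detected (48%), the pooled result is 98 + 12 = 110/123 = 89% (83 to 94%).
- q = 42% gives 52 non-acidic and 71 acidic samples. If 39 of 52 are detected (75%), the pooled result is 71 + 39 = 110/123 = 89% (83 to 94%).

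The novel strip's planned result is identical in the two cases, although detection in the samples of interest is 48% in one and 75% in the other.

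**What the planned pH-strip figure adds.** Under the same assumptions, L = (S_new − S_pH) / (1 − S_pH). In the first case this is (110/123 − 98/123) / (25/123) = 12/25 = 48%, so the quantity can be recovered. Two limits apply.
- If the novel strip reads only a share a of acidic samples as positive, the recovered value becomes L − (1 − a)(1 − q)/q. Each percentage point of acidic samples missed lowers it by 0.80/0.20 = 4 points at q = 20%, and by 0.58/0.42 = 1.4 points at q = 42%.
- Two separate intervals give no interval for L and ignore the pairing. In the first case they are 83 to 94% and 98/123 = 80% (72 to 86%), which overlap, although all 12 discordant pairs favour the novel strip (exact McNemar p = 2 × 0.5^12 = 0.0005).

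**Precision of the direct estimate.** At about half detected: 12/25 = 48% (28 to 69%), 18/37 = 49% (32 to 66%), 26/52 = 50% (36 to 64%), 31/62 = 50% (37 to 63%), for q of 20, 30, 42 and 50%.

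**The case against.** The best defence is that accuracy of the combined strip in all tube-fed patients is a legitimate estimand. Study aims asks for sensitivity and specificity without a stratum, and clinicians will use the strip on every aspirate. That stands: the pooled figure is worth reporting.

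The second defence is that the comparator's sensitivity is planned on the same aspirates, so at q = 20% and L = 50% the report would show 90% beside 80%. A careful reader would see that half of the possible gain was achieved. This largely stands and rules out saying that the planned results cannot answer the question. It does not supply a confidence interval. It also depends on every acidic sample turning the novel strip positive, while the protocol itself calls the pH reading subjective and leaves novel-strip positivity to the manufacturer's recommendations.

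Third, subgroup tables are often left to an SAP, and one may exist. That lowers the weight of the point. The primary outcome, however, is fixed in the protocol, and as written it does not directly address the stated objective.

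Two stronger readings are tempting and unsupported. A reader might infer that antacid use will not be recorded; but the protocol itemises none of its clinical characteristics, so its silence on one shows nothing. A reader might also take the objective to be performance in antacid users; but antacids appear as the rationale, and the objective names non-acidic aspirates. The standard strip identifies those samples directly, with no need for a medication record.

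**Conclusion.** The point holds in a limited form. The planned estimate pools samples that say nothing about lipase with those that do, and the samples named in the objective get no estimate of their own. The size depends on an unknown q: at L = 50% the pooled figure is 90% when q = 20% but 79% when q = 42%, so a poor lipase component is well hidden only when non-acidic aspirates are few. These figures rest on assumed q and L, on about 123 evaluable patients, and on full positivity of acidic samples.

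This is a mismatch between objective and planned estimate that already-planned data can repair. It does not invalidate the design.

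**What to change.** Add to Statistics, in substance: *Sensitivity of the novel strip with 95% CI will be reported in aspirates from tubes confirmed to be in the stomach with a standard-strip pH above 5.5. The paired difference in sensitivity between the two strips, with 95% CI, will be reported over all confirmed gastric aspirates. Conclusions about non-acidic aspirates will rest on these two estimates.* Keep the overall sensitivities as planned. If the SAP already contains these analyses, a cross-reference is enough.

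Naming acid-suppressing medication among the clinical characteristics would be a useful but optional descriptive addition.

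The cost is a sentence or two of text and one table, with no extra patients, samples or procedures. The stratum estimate will be less precise than the pooled one, with an interval of about 28 to 69% on 25 samples or 36 to 64% on 52 when half are detected. The report should show that imprecision.

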**2. Study of test’s ability to predict lung placement**

In addition to this diagnostic accuracy study a separate analysis of the novel test will be undertaken to assess the accuracy of the test in the presence of lung aspirates. This study will be undertaken as NG placement in the lung is an extremely rare event and unlikely to occur in the population in study 1. However, lung placement is a major cause of morbidity and mortality in the use of NG tubes and therefore this study will ensure that the new test is reliable able to recognise lung intubation. Lung aspirates will be obtained from patients who are intubated for elective surgery. Correct tube placement will be confirmed with capnography and therefore it is reliable that aspirates from the tubes are from the lung. The aspirates will be tested with the novel test strips in the same method as for study 1 and used to determine sensitivity. 50 samples will be tested.

*Subject selection and setting*

Patients intubated for elective surgery

*Exclusion Criteria*

- Patients under the age of 18 years
- Prisoners
- Patients sectioned under the Mental Health Act

**Human factor analysis**

*Subject selection and setting*

25 participants will be recruited from Imperial Healthcare NHS Trusts. Due to the nature of the task involved in using the pH strips, professionals with visual impairments, such as colour blindness, will be excluded for the evaluation cohort. The sample size is in keeping with ISO 62366 (2008) guidelines to ascertain perceivable usability defects and qualitative analyses. Simulation tests will be performed at St. Mary’s hospital facilities.

*Inclusion Criteria*

Professionals with at least one year of experience in the use of pH strips to ascertain nasogastric feeding tube position.

*Exclusion Criteria*

- Visual impairments including colour blindness
- Patients under the age of 18 years
- Patients who are unable to sign consent.
- Patients who do not provide consent.

*Simulation Protocol*

During the simulation professionals will undertake a set of scenarios that involve interaction with lipase/pH test strip. Participants will be asked to simulate the procedure of NG tube positioning and the use of lipase/pH test strip. Time and error of performances will be tracked, and standardised scales will be used to assess their experience with the lipase/pH strip (see appendix).

**Consent**

Participants will be identified by the clinical team according to their eligibility on the research study. For patients who can consent, the research study will be fully explained to them. They will be given the patient information leaflet to read, what has been mentioned by the researcher. Consenting participants will be given enough time to think and decide to participate on the study. These participants will be requested to sign the consent prior obtaining any demographic questions. They can withdraw anytime freely from the study without giving reason and no prejudicial effect on their subsequent treatment.

For patients who have been determined to lack the capacity to consent for themselves through the Mental Capacity Act (2005), a Personal/Nominated Consultee will be consulted. The Personal/Nominated Consultee will be the one to decide if the patient would have no objection to taking part in the study, and therefore will be given a Consultee Information Leaflet. They will be given time to think and decide their actions. If they have deemed that the patient will have no objections to participate, they will then sign a Consultee Declaration Form. During the course of the study, if or when the patients gain back their capacity to consent, they will be consented by the researchers following the process of consent for consenting participants. They can withdraw anytime freely from the study without giving reason and no prejudicial effect on their subsequent treatment.

**Adverse Events**

The sample is to be collected from the nasogastric tube. Aspiration will be performed by a trained healthcare professional. Privacy and dignity will be ensured to the patient at all times during the study. As required samples are gastric aspirate that are collected as part of the patients usual clinical care we do not foresee any safety issues to arise from study participation. Results from the lipase/pH test strip will not be used to direct clinical care.

**Ethics**

Appropriate ethical approval will be sought from the xxx Research Ethics Committee. We have previously been granted ethical approval for both a pilot study of the clinical test prototype (REC ref 10/H0724/76) and for qualitative research into proactive risk assessment of hazards associated with NG tubes (REC ref 09/H0724/76).

**Indemnity**

Imperial College London holds negligent harm and non-negligent harm insurance policies that apply to this study.

**Confidentiality**

The Chief Investigator will preserve the confidentiality of participants taking part in the study and is registered under the Data Protection Act.

**Audits**

The study may be subject to inspection and audit by Imperial College London under their remit as sponsor and other regulatory bodies to ensure adherence to GCP and the NHS Research Governance Framework for Health and Social Care (2nd edition).

**Publication Policy**

The workshop outputs will be written up for peer-reviewed journals or submitted to academic conferences.

**Funding**

The funding for this body of work will be from Innovate UK and Ingenza. [Grant number]

Appendix

1. **Information About You**

We would like to collect some information about you, and your expertise in the use of pH Strips to checking the position of the nasogastric feeding tube.

| 1. Your place of work… *(please, mark all that apply)*  - Primary care - GP surgery - Primary care - Social services - Secondary care - NHS Hospital Trust - Secondary care – other, please specify: ________________________ - Tertiary care |
| --- |
| 1. Level of experience… *(please, mark all that apply)*  - Doctor - Nurse - Paramedic - Pharmacist - Physiotherapist - Dietician - Other, please specify: _______________________________ |
| 1. Your gender is  - Male - Female - I prefer not to say |
| 1. Are you used to checking the position of the NG tube with pH strips? *(please, mark only one box)*  - Not at all. - Yes, but only when I have to. - Yes, on regular basis. |
| 1. Do you suffer from colour vision deficiency (colour blindness)? *(please, mark only one box)*  - No - Yes |
| 1. Have you received training in the use of pH strips and nasogastric feeding tubes?  - Not at all. - Yes, I received informal training at _____________________Year: - Yes, I received formal training at _______________________Year: |
| 1. How many years of experience do you have using pH strips to check NG tube positioning? _______ |
| 1. Your Age:  - 18-24 years old - 24-35 years old - 36-45 years old - 45-54 years old - >54 years old |

1. **How much trust do you have in the use of [***the new pH Strips***] to check the nasogastric feeding tube positioning?**

**Instructions**: For each of the following statements, mark one box that best describes your trust in the use of [new pH Strips] to check nasogastric tube position **from 1 (strongly disagree) to 7 (strongly agree)**

| - - 1. I am totally comfortable working with [new pH Strips]. | 1 | 2 | 3 | 4 | 5 | 6 | 7 |
| --- | --- | --- | --- | --- | --- | --- | --- |
| - - 1. I feel very good about how things go when I use [new pH Strips]. | 1 | 2 | 3 | 4 | 5 | 6 | 7 |
| - - 1. I always feel confident that the right things will happen when I use [new pH Strips]. | 1 | 2 | 3 | 4 | 5 | 6 | 7 |
| - - 1. It appears that things will be fine when I use [new pH Strips]. | 1 | 2 | 3 | 4 | 5 | 6 | 7 |
| - - 1. I believe that most [new pH Strips] are effective at what they are designed to do. | 1 | 2 | 3 | 4 | 5 | 6 | 7 |
| - - 1. A large majority of [new pH Strips] are excellent. | 1 | 2 | 3 | 4 | 5 | 6 | 7 |
| - - 1. I think most [new pH Strips] enable me to do what I need to do. | 1 | 2 | 3 | 4 | 5 | 6 | 7 |
| - - 1. My typical approach is to trust new [new pH Strips] that I have never used before until they prove to me that I shouldn’t trust them. | 1 | 2 | 3 | 4 | 5 | 6 | 7 |
| - - 1. I usually trust a pH strip outcome until it give me a reason not to trust it. | 1 | 2 | 3 | 4 | 5 | 6 | 7 |
| - - 1. I rely on alternative bedside methods (not x-ray) for confirmation of nasogastric tube placement in addition to aspirate pH determination | 1 | 2 | 3 | 4 | 5 | 6 | 7 |

*The above 10 statements are adapted from recent research on trust in technology. See for reference– Mcknight, D. H., et al. (2011). Trust in a specific technology: An investigation of its components and measures.*

1. **Perceived experience in use**

The following statements have been used by others to assess the perceived experience in the use of a tools.

In this case, we will ask to you to answer the questions in relation to the use of **current** **[***the new pH Strips***] to ascertain NG tube positioning**.

Please follow the instructions and fill in the questionnaire

**Instructions:** For each of the following statements, mark one box that best describes your overall experience with **current** **[new pH Strips] to ascertain NG tube positioning***:*

|  | Strongly Disagree |  |  |  |  |  | Strongly Agree |
| --- | --- | --- | --- | --- | --- | --- | --- |
| 1. [new pH Strips] capabilities meet my requirements | 1 | 2 | 3 | 4 | 5 | 6 | 7 |
| 1. [new pH Strips] are easy to use | 1 | 2 | 3 | 4 | 5 | 6 | 7 |

* See for reference – Finstad, K. (2010) The usability metric for user experience.

1. **Expectations**

By assuming the reliability of **[***the new pH Strips***]**, please rate your agreement with the following statements.

|  | Strongly Disagree |  |  |  |  |  | Strongly Agree |
| --- | --- | --- | --- | --- | --- | --- | --- |
| I believe that I will prefer to use an dual functioning gastric acid and [*the new pH Strips*] instead of a pH strip to ascertain the NG tube positioning | 1 | 2 | 3 | 4 | 5 | 6 | 7 |
| I believe that I will have a lowered need to use X-ray to confirm a NG tube positioning if I will have [*the new pH Strips*] | 1 | 2 | 3 | 4 | 5 | 6 | 7 |

1. **Your intention to use [***the new pH Strips***]***

***Instructions:*** mark one box that best describes your intention of use.

|  | Strongly Disagree |  |  |  |  |  | Strongly Agree |
| --- | --- | --- | --- | --- | --- | --- | --- |
| I would like to use **[***the new pH Strips***]** if I need to perform an anaemia test | 1 | 2 | 3 | 4 | 5 | 6 | 7 |

* See for reference– Lee, S. and Koubek R. J. (2010). Understanding user preferences based on usability and aesthetics before and after actual use.

1. **Your likelihood to recommend [***the new pH Strips***]****

| ***Instructions*** mark one box from 10 (**Extremely like)** to 0 (**Not at all likely)**  How likely is it that you would recommend to your hospital and your colleagues the use of the **[***the new pH Strips***]** to check the placement of NG tube? | | | | | | | | | | | | |
| --- | --- | --- | --- | --- | --- | --- | --- | --- | --- | --- | --- | --- |
| Extremely  likely | **10** | **9** | **8** | **7** | **6** | **5** | **4** | **3** | **2** | **1** | **0** | Not at all likely |
|  |  | |  | |  | | | | | | |  |
|  | [figure not shown] | | [figure not shown] | | [figure not shown] | | | | | | |  |

** See for reference - Reichheld, F. (2003). One Number You Need to Grow.

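### The only intention-to-use item in the human-factor questionnaire asks about an anaemia test, so its answers cannot show intention to use the strip for nasogastric tube checks

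*Protocol*

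**What the plan says.** The third of the Study aims is to observe use of the lipase-based strip in simulation and to "analyse the perceived usefulness of this test from professional perspective". The Human factor analysis section sets out how: "25 participants will be recruited from Imperial Healthcare NHS Trusts", and "During the simulation professionals will undertake a set of scenarios that involve interaction with lipase/pH test strip". Time and errors are tracked, and "standardised scales will be used to assess their experience with the lipase/pH strip (see appendix").

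The Appendix is therefore the data-collection instrument for this aim. Two of its sections matter here.

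- **Your intention to use.** The instruction is to "mark one box that best describes your intention of use". One statement follows, rated 1 to 7: whether the respondent would like to use the new strips "if I need to perform an anaemia test".
- **Perceived experience in use.** Two statements are rated 1 to 7. The instruction asks about "your overall experience with current [new pH Strips] to ascertain NG tube positioning", and the introduction above it uses the same combination of *current* and new strips.

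**The concern.** The intention item names the right product and the wrong use. The Protocol describes a strip that turns positive in the presence of acid or gastric lipase and is intended to confirm that a feeding tube is in the stomach. Anaemia is mentioned nowhere else in the document.

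An answer to the item as worded has no single meaning. A low score may mean that the respondent would not adopt the strip, or simply that it is not an anaemia test. A high score may mean that the respondent took the wording for a misprint and answered about tube position. The two readings cannot be separated afterwards, so the result says nothing reliable about intention to use. Because it is the only item in its section, no companion item can stand in for it.

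The experience section has a milder problem. Respondents must have at least one year's experience with pH strips, so *current* strips could suggest the ones they already use on the ward, while the bracketed name points to the new ones.

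**Working it through.** No arithmetic in the Protocol bears on this point: it depends on no error rate, power or effect size. The check sets the wording of each questionnaire section against the purpose stated in Study aims and Human factor analysis, and counts the items affected.

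**Step 1. What the form is for.** The Human factor analysis section says that the appendix scales assess experience with the lipase/pH strip. The simulation has professionals simulate tube positioning with that strip.

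**Step 2. What each section asks.**

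| Appendix section | Rated items | Product named | Use named | Finding |
|---|---|---|---|---|
| Trust | 10 | New strips, in heading and instruction | Tube position, in heading and instruction | Not affected |
| Perceived experience | 2 | New strips in both items; *current* added in introduction and instruction | Tube position, in introduction and instruction | Ambiguous stem |
| Expectations | 2 | New strips | Tube position, in both items | Not affected |
| Intention to use | 1 | New strips | Anaemia test | Wrong use |
| Recommendation | 1 | New strips | Tube placement | Not affected |

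**Step 3. Count.** Rated items: 10 + 2 + 2 + 1 + 1 = 16. One of 16 is unusable as worded, and it is 1 of 1 in its section. Two of 16 sit under an ambiguous stem, although neither item is itself worded for the wrong product. The remaining 16 − 1 − 2 = 13 are untouched by either wording error.

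**Step 4. Responses.** With 25 participants and one intention item, 25 × 1 = 25 planned responses are affected if every participant completes the form uncorrected.

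**Step 5. Placeholder or not.** Product names in the Appendix stand in square brackets, as text still to be filled in. The anaemia phrase and the word *current* both lie outside the brackets. Filling in the product name would leave both in place.

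**The case against.** The strongest reply is that this is one slip in a secondary questionnaire. The neighbouring items are correctly worded: preference over a pH strip for tube positioning, reduced need for X-ray, and likelihood of recommending the strip for checking tube placement. Together with the trust items and the recorded times and errors, they still serve the aim. The bracketed names also suggest a form not yet final. All of this stands, and it is why the point is minor. It does not rescue the intention item, whose error would survive completion of the brackets.

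Three stronger readings are tempting, and the document does not support them.

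- A reader might infer that the experience scale fails to measure the lipase strip, or mixes ratings of two products. Both rated items name the new strips without *current*, the stem ties them to tube positioning, and the simulation describes handling only the lipase/pH strip. Ambiguity is shown; mixing is not.
- A reader might infer that respondents will disagree with the anaemia item and push the result downwards. Some may correct it silently. The direction is unknown, and the defect is that the answers cannot be interpreted.
- A reader might add the age bands, printed as "18-24 years old - 24-35 years old - 36-45 years old - 45-54 years old", which overlap at 24 and 45. That is true but clerical: the Protocol states no analysis by age for these professionals, so no result is shown to depend on it.

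**Conclusion.** Wrong as written, of minor severity. Used uncorrected, the form gives no interpretable measure of intention to use the strip for checking nasogastric tube position, so this one strand of the third aim is lost. The experience scale is ambiguous about the product being rated, and no more than that.

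The diagnostic-accuracy study and the lung-aspirate study do not use the questionnaire and are untouched.

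The conclusion rests on two assumptions: that the Appendix is the form participants would receive, and that it is not corrected beforehand. If it was corrected before use, only the Protocol text needs to be brought into line.

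**What to change.** In the intention section, replace the closing clause with *if I need to check nasogastric tube position*. In the experience section, delete *current* in both the introduction and the instruction. There is no need to give the scale once per strip: that would add a comparison with the standard strip which the Human factor analysis section does not plan.

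The cost is a correction of a few words to the form before first use, with no change to sample size, procedures or analysis. If any forms have already been completed with the anaemia wording, those answers should not be reported as intention to use the strip for tube position.
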